### Sample size

With 400 patients (600 eyes) we expect 170 composite time-to-event focal events signifying progression to late AMD. Focal events include drusen regression, early-onset neurosensory atrophy or choroidal neovascularisation, assuming 20% dropout and different 50%/20% unilateral/bilateral event rates, and conservatively maintained at 20% at the point of development of an event in the study eye(s) based on drusen regression in 26% of drusen over 5-year follow-up [35], and an overall conversion rate of 32% in unilateral neovascular AMD eyes over 2 years [35], which is in line with other literature [36]. Lifetable analysis showed that 170 events would be expected with these rates and 20% 3-year dropout. This was robust in a subsequent calculation over altered variable follow-up durations and employing higher observed event rates. For event modelling projects there is no statistical null hypothesis and so sample size calculations are not based on power. Instead, a rule of thumb is used that ten events (or ten non-events, if smaller) are needed per baseline-visit candidate predictor accommodated in the full model. Therefore, the initial model development stage after 360-eye follow-up (102 events) will accommodate ten identified structural biomarkers and potential genetic and phenotypic predictors. The 240-eye model (68 events) validation stage includes: calibration and discrimination and provides an informative narrow 95% confidence interval for C-index widths of ~±0.08.

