### Plan for statistical analysis

The cohort will be divided 3:2 into a Cox model development stage (240 patients; 360 eyes; 102 primary endpoints) allowing ten (102/10) candidate predictors [33] and a validation stage (160 patients; 240 eyes; 68 primary endpoints), to enable the identification of the important predictors (primary study outcome) and their relative importance, and other key supportive outcomes including the area under the ROC curve with sensitivity and specificity estimates. After full recruitment, the patients defining these stages will be identified. Stage 1 modelling will begin prior to full follow-up. Candidate predictors will include identified structural biomarkers and potential genetic and phenotypic predictors. The initial full model will be a comparator and simplified with backwards elimination [37]. Continuous predictors will be included as fractional polynomials [38]. Models will include a unilateral/bilateral main effect to improve transportability to samples with an alternative case-mix. Intra-patient between-eye correlation will be accounted for with marginal models, with ‘eye’ the unit of prediction. Validation in Stage 2 will include calibration of the performance of the Stage 1 model [39] and discrimination via the C-index with sensitivity, specificity and predictive values, and assessment of any over-fitting bias.

External transportability of the model will involve meta-analytic methods. Fast progressors and early conversion to AMD will be explored, and short-term changes in predictors.

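### The ten-predictor budget counts each predictor as one parameter, so fractional polynomials and the laterality term take the full Cox model below ten events per parameter

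*Protocol article*

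**What the plan says.** The Sample size section of the protocol article sets aside power and sizes the study by a rule of thumb: "ten events (or ten non-events, if smaller) are needed per baseline-visit candidate predictor accommodated in the full model". The expected yield is given as "With 400 patients (600 eyes) we expect 170 composite time-to-event focal events signifying progression to late AMD".

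The Plan for statistical analysis section then splits the cohort: "The cohort will be divided 3:2 into a Cox model development stage (240 patients; 360 eyes; 102 primary endpoints", and reads the budget off directly, "allowing ten (102/10) candidate predictors". The same paragraph makes two further commitments about the model:

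- "Continuous predictors will be included as fractional polynomials". No maximum degree is given, and the number of continuous predictors is not stated.
- "Models will include a unilateral/bilateral main effect to improve transportability". Whether this term is one of the ten is not stated.

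On what the ten cover, the Sample size section says the development model "will accommodate ten identified structural biomarkers and potential genetic and phenotypic predictors". The Plan for statistical analysis section lists the same categories as the content of the candidate predictors, which reads as ten in all. It also lets the statistical analysis plan (SAP) change the number of candidate predictors according to how many events are observed.

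The Primary outcome section defines the primary outcome as the candidate predictors that remain in this Cox model after backwards elimination.

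**The concern.** An events-per-predictor rule protects a model only if each predictor costs one coefficient. A fractional polynomial costs more: one extra coefficient for each further term, and the data-driven choice of powers also uses information. A binary laterality term costs one parameter. The budget of ten is fully spent before either is counted.

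The full model is where this matters, because the stated rule applies to the full model and backwards elimination starts from it. Eliminating terms later does not refund the degrees of freedom spent in the search. As events per candidate parameter fall, the retained set depends more on the particular sample and the retained coefficients tend to be too extreme, so predicted risks are too spread out at validation. In many studies that would affect a secondary model. Here the retained set is the primary outcome, and its weights and area under the ROC curve are the key supportive outcomes.

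**Working it through.** **Inputs from the article.** 170 expected events in 600 eyes; a 3:2 split; ten events per candidate predictor; ten candidate predictors; fractional polynomials for continuous predictors; one unilateral/bilateral main effect.

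**Inputs assumed.** Degrees of freedom (df) per continuous predictor are not in the article. The range used is 1 (linear), 2 (first-degree polynomial with its power counted, or second-degree with coefficients only) and 4 (second-degree with both powers and both coefficients counted). The number of continuous predictors is also not given; 0, 5 and 10 are shown. Laterality is taken as an eleventh term.

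**Reproducing the plan's figures.** Development events = 170 × 3/5 = 102. Validation events = 170 × 2/5 = 68. Budget = 102/10 = 10.2, so ten predictors with 0.2 of a predictor to spare. All match the article. The 170 is taken as given; the article derives it by "assuming 20% dropout and different 50%/20% unilateral/bilateral event rates". Assuming 200 unilateral and 200 bilateral patients, simple life-table versions of that calculation gave roughly 161 to 168 events when run over the same period as the event rates, so it is a reasonable starting point.

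**Events per candidate parameter.** Parameters = (linear or binary predictors × 1) + (continuous predictors × df) + 1 for laterality. Ratio = 102 / parameters.

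| Full model | Parameters | Events per parameter |
|---|---|---|
| Ten single-parameter terms, laterality among them | 10 | 10.2 |
| Ten linear + laterality | 10 + 1 = 11 | 9.3 |
| Five continuous at 2 df, five linear or binary, laterality | 10 + 5 + 1 = 16 | 6.4 |
| Five continuous at 4 df, five linear or binary, laterality | 20 + 5 + 1 = 26 | 3.9 |
| Ten continuous at 2 df + laterality | 20 + 1 = 21 | 4.9 |
| Ten continuous at 4 df + laterality | 40 + 1 = 41 | 2.5 |

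Only the first row reaches ten. It requires every predictor to cost one parameter and laterality to be inside the ten.

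**What the budget would hold.** At ten events per parameter with laterality counted, 10.2 − 1 = 9.2 df remain. That is four continuous predictors at 2 df (9.2/2 = 4.6) or two at 4 df (9.2/4 = 2.3). Each leaves one df for a binary predictor within a total of 10.

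**What keeping all ten would need.** Development events = 10 × 21 = 210 at 2 df, or 10 × 41 = 410 at 4 df. Against the planned 102, the first is about double and the second exceeds the 360 development eyes. More events is therefore not a realistic remedy; fewer or simpler terms is.

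**Illustration of the consequence.** Take approximate shrinkage = LR/(LR + p), with p the number of parameters, LR = −360 × ln(1 − 0.696 × R²), and R² an assumed Nagelkerke value. The factor 0.696 is the maximum from a binary approximation with 102 events in 360 eyes. At R² = 0.15, LR = 39.7, giving 0.78, 0.65 and 0.49 for 11, 21 and 41 parameters. At R² = 0.30, LR = 84.3, giving 0.88, 0.80 and 0.67. These show direction and rough scale only: the R² values are not in the article, the formula borrows a binary outcome for a Cox model, and correlated eyes are treated as independent.

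**The case against.** The strongest reply is that the stated rule is met. It is written per candidate predictor, not per parameter, and 102 events for ten predictors satisfies it. That stands: a reader might infer that the plan breaks its own rule, but the text does not support this. The only possible literal breach is laterality as an eleventh term, which gives 9.3, a trivial departure from a rule of thumb. The criticism is that the rule is counted in a unit that does not protect this model.

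Second, 2.5 is a floor. It needs all ten predictors to be continuous, second-degree and charged 4 df. The Primary outcome section plans ROC curves only for biomarkers that are not binary, so some binary ones are expected, and the Prospective cohort analysis section adds smoking history, medical history and genotype. A polynomial search can also end in a straight line, although the search still uses degrees of freedom. This too stands, and 2.5 should not be quoted as the operating condition.

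Third, a reader might infer from the Sample size section that genetic and phenotypic predictors come on top of ten biomarkers. That is one reading; the Plan for statistical analysis section points to ten in all. Extra predictors are in any case not needed to reach 2.5, since 41 = 10 × 4 + 1 contains none.

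Fourth, a reader might infer that Stage 2 validation is the only guard against over-fitting. It is not. Candidates are to be listed in the SAP before predictors and outcomes are joined. The oversight committee approves the final version. The OCT biomarkers are derived and tested in the separate retrospective dataset, and the full model is kept as a comparator. These measures limit which predictors enter, but not how many parameters each one uses, and the article states no shrinkage of the Stage 1 coefficients.

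Fifth, polynomial degree and penalisation are ordinary SAP content, and that document is not shown. Their absence from the article is no fault. However, the 102/10 budget and the commitment to fractional polynomials are both fixed in the article, and the one stated adjustment responds to observed events, not to degrees of freedom. An SAP that followed the article would carry the miscount forward.

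**Conclusion.** The point holds in a limited form. The budget is fully used at ten one-parameter predictors, so any continuous predictor entered at more than 1 df, or laterality as an eleventh term, takes the full model below ten events per parameter. For ten predictors plus laterality the supportable range is 9.3 down to 2.5: 6.4 with half of them continuous at 2 df, and 4.9 with all of them. The position within that range depends on the number of continuous predictors and the polynomial degree, neither of which is stated. The figures take the 102 events as given; if fewer accrue, the provision for changing the number of predictors can offset the shortfall, though only in units of predictors.

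The consequence is a raised risk of unstable selection and over-fitted coefficients in the analysis that defines the primary outcome. The article does not support the stronger conclusion that the model will be miscalibrated. This is an inexpensive improvement to make before modelling begins, not a flaw that invalidates the design.

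**What to change.** - In Sample size and Plan for statistical analysis, state the budget as candidate parameters: about 10 df at 102 events, rescaled to the events achieved. Count laterality and all fractional-polynomial terms within it, and make the provision for changing the number of predictors work in the same unit.
- Cap the polynomial degree so that the full model stays within the budget. At 102 events, laterality, four continuous predictors at 2 df and one binary predictor fit exactly (1 + 8 + 1 = 10), as do laterality and nine linear terms.
- Prespecify a uniform shrinkage factor or a penalised Cox fit for the Stage 1 coefficients.
- Reword the Sample size sentence so that genetic and phenotypic predictors clearly fall inside the total.

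The cost is wording, plus fewer or simpler terms in the full model; some non-linear effects may go unmodelled. No extra patients or visits are needed. Because Stage 1 modelling is to start before follow-up is complete, the change should be in place before predictors and events are first joined for the development patients. Later, the choice of terms could be influenced by the data.

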### Trial management and monitoring

The study is overseen by a TSDC who will ensure the overall study integrity by monitoring progress, investigating and reviewing reports from the trial management group (TMG). It will consist of an independent Chair, independent retinal Specialists, and patient representatives. As there is no intervention or blinding of results it will also take on the role of a Data Monitoring Committee and will monitor the trial data to ensure accuracy, patient safety and ethical conduct, and will monitor recruitment data, adverse events, emerging external evidence, sample characteristics, primary outcomes and make recommendations regarding any interim analysis. The TSDC will meet yearly for the first 3 years.

Study documents, site initiation and training and day-to-day running of the study and monitoring of sites is being managed by the Clinical Trial Project Manager. A trial management group (TMG) (Chief Investigator, co-applicants, trial manager and other key members of the group) oversee the development and operation of the study, monitor and maintain recruitment rates. The TMG participate in teleconferences fortnightly to discuss the ongoing progress and meet annually to discuss the study progress as a whole.

The Trial Executive Group (TEG), chaired by the Chief Investigator, will collate and lead planning of publications encompassing data from all Collaborators. It is anticipated that each paper will have a writing committee involving the Co-Investigators who will then form the listed authors for the paper. Consensus will be sought from the TEG on authors and authorship order with a majority vote of TEG if needed being final.

### Protocol amendments

Version 1.1 was used when recruitment started (28 October 2019) and version 3.2 is currently in use. The main changes have been to the minimum change of follow-up. This has changed from 3 years to a minimum of 1. This has been due to the disruption of set up and recruitment during the COVID-19 pandemic. We have also changed the definition of a focal event. This was due to the original definition being too sensitive and picking up more than the relevant events. Frequency of microperimetry tests was increased to provide additional data on the focal events. Visit windows were also introduced to aid flexibility for participants and study teams, and the taking of blood samples was changed to allow it in any of the first 4 visits.

## Discussion

Using the retrospective element of this study we will identify OCT biomarkers through ML, which predict progression of intermediate to late AMD. We will evaluate these OCT biomarkers in the prospective natural history study described here. We will also create a reference annotated dataset of OCT images that may be of use for future ML projects. Focal events as defined here will enable us to stratify the prospective cohort into fast and slow progressors. In addition, this study will extensively phenotype this cohort of patients with exploratory tools, i.e. adaptive optics as well as the functional measures of microperimetry and also OCT angiography and autofluorescence imaging to determine the most sensitive biomarkers of progression. The aim is that the results of this project will provide a comprehensive evaluation of imaging and genetic biomarkers associated with intermediate AMD progression. This may inform a better understanding of underlying cellular and molecular processes associated with AMD pathogenesis. It will also allow the generation of a probabilistic risk score to aid patient stratification and management on an individualised and population-based level.

The clinical set-up for this study was slower than anticipated due to the COVID-19 pandemic halting recruitment at many sites for months. UK patients from referral sites were also reluctant to travel to the two main UK sites, Southampton and Moorfields for detailed focal event phenotyping. An additional challenge was working with different ethics regulations in different countries. For example, in Switzerland we were not allowed to recruit patients over the age of 90 which meant for consistency across all sites we did not recruit patients at any site over the age of 90. Budget constraints meant we could not employ a full clinical trial centre for trial oversight which was also challenging in terms of trial management.

Features of national healthcare systems have to be considered: Most patients were recruited from tertiary hospital sites which meant that many patients already had advanced AMD in their second eye. Thus, our estimate that we will recruit two eyes from around 50% of patients appears optimistic. Many patients with intermediate AMD would not be followed up routinely in the hospital eye service in the UK so they welcomed being included in a study were they would be observed for evidence of advancing to late-stage AMD. Consequently, retention in the study has been higher than expected. Indeed, wet AMD has been diagnosed at an early asymptomatic stage in several patients allowing early treatment to be instituted.

## Summary

### What was known before

Risk factors for AMD progression are known and AMD risk calculators available.However the sensitivity of risk calculators for AMD progression is poor.

### What this study adds

This study will combine data from a large-scale retrospective analysis of OCT images with a prospective study of intermediate AMD patients.Using machine learning of high-resolution three-dimensional retinal images and deep phenotyping this study will aim to identify sensitive and objective markers of progression of intermediate AMD.Description of the temporal sequence of morphological changes in each layer of the retina, RPE and choroid, under simultaneous evaluation of functionality, during progression of AMD and ageing in the retina.Correlation of imaging markers with the genetic profile of each individual in the prospective study and endophenotypes described.Mechanistic insight should be gained on the aetiological factors that cause intermediate AMD to progress.The potential for future treatment to be individualised to each patient, allowing for treatment to be optimised.The potential for improved stratification of patients in clinical trials.

## Data Availability

Data from this project will be referenced and linked to in papers published from this project in peer-reviewed journals. This data will include 1. The atlas of central retinal ageing and patient specific risk model. This will be available via websites hosted by Imperial College London. 2. Relevant imaging datasets will be made available via the Vienna Reading Center where the data will be stored via application to this research consortium who will be custodians of the data. 3. Genotype data. This will be stored at the European Genome-phenome Archive (EGA) (https://www.ebi.ac.uk/training/online/course/genomics-introduction-ebiresources/ europeangenome-phenome-archive-ega). Small datasets derived from this work may also be held on ePrints Soton, for example those bits of data directly mentioned in a journal paper. These datasets can either be openly available or available on request (for example if ethics clearance is required). The University of Southampton can issue DOIs for these datasets and they will be held for a minimum of 10 years since the last access as per the University’s Research Data Policy.
